**PARTⅠ: OUTLINE OF APPLICATION**

**﹡Mandatory field must be filled in. Put down “NA” if not applicable.**

1. Name of Study

| 1.1 | Scientific title (*should include study design, name of intervention, condition being studied and study outcomes*) | |
| --- | --- | --- |
| ﹡A randomized pilot trial comparing position emission tomography (PET)-guided dose escalation radiotherapy to conventional radiotherapy in chemoradiotherapy treatment of locally advanced nasopharyngeal carcinoma | |
| 1.1.1 | Research protocol number | ﹡XYFYLW2009001 |
| 1.2 | Short Title (for lay public / easy quote) | |
|  | ﹡PET/CT guided radiotherapy | |

**5. Parallel Ethics Review for Cross-cluster Study**

| 5.1 | Has the protocol been reviewed by another Cluster REC/IRB? | N/A(not planned for Cross-cluster involvement) |
| --- | --- | --- |
|  | **(If yes, please state the Cluster REC/IRB in Item 5.1.1 in supplementary sheet)** | |
| 5.1.1 | What is the REC decision?(Provide proof if available) | Don’t know |

**6. Milestones**

| 6.1 | Proposed study start date: | 2 / 2009 (mm / yyyy) ﹡ |
| --- | --- | --- |
| 6.2 | Proposed study end date or date of last follow-up of all recruited subjects, whichever is later: | 4 / 2014 (mm / yyyy) ﹡ |
| 6.3 | Expected final report date to Cluster REC: | 4 / 2014 (mm / yyyy) ﹡ |

**7. Brief Summary of Study** (＜500 words, use language that can be understood by laypersons)

| This pilot trial is designed to determine whether PET/CT-guided radiotherapy dose escalation can improve local control while minimizing toxicity for the treatment of locally advanced nasopharyngeal carcinoma. One distinct advantage of PET/CT in radiotherapy planning is its potential to improve target identification, reducing intra-observer and inter-observer variability. We hypothesize that the use of PET/CT in treatment planning can improve dose-escalation radiotherapy for NPC which in turn can improve therapeutic efficacy while reducing toxicity. We prespecified our primary subgroup analysis on the basis of PET / CT positioning and SMART-IMRT. We also did prespeciﬁed secondary subgroup analyses based on sex, age, and c[linical stages](dict://key.0895DFE8DB67F9409DB285590D870EDD/clinical stages). For all subgroup analyses, we used the Kaplan-Meier method to calculate the actuarial rates of local control, DFS and OS. The χ2 test was used for comparing incidence rates and categorical variables and Student’s t-test was used for comparing the means of continuous variables, designated to be significant at p<0.05. PET-CT fusion may have significant impact on staging and radiotherapy treatment delineation in NPC. PET/CT-guided dose escalation radiotherapy appears to be well-tolerated. The SMART-IMRT technique to enhance BED of GTV, combined with concurrent chemotherapy, is completely feasible for local advanced NPC. |
| --- |

**8. Major Ethical Issues** (＜500 words, use language that can be understood by laypersons)

| We considered that the use of 18F-FDG-PET/CT may slight impact on the surrounding environment, especially in the patient's excreta.  Control Measures: All patients were required to sign an informed consent form before proceeding to clinical trials. Patient’s PET/CT scanning in strict accordance with PET/CT examination processes. Patients need to wait to check in a separate waiting rooms or wards in the hospital setting PET-CT centers. All patient’s excrement (feces, urine, etc.) were separately destroyed. Patients were isolated for observation to a specified time after the inspection is completed. given radiation dose detection before return to the general ward. |
| --- |

**PART Ⅱ: STUDY DETAILS**

**9.** Scientific basis

| 9.1 | Background, current evidence and key references: | | |
| --- | --- | --- | --- |
|  | Nasopharyngeal carcinoma (NPC) differs from other head and neck malignancies in terms of its epidemiology, pathology, and treatment outcomes. It is endemic in China and is one of the major public health problems. Concurrent radiotherapy and chemotherapy is the primary treatment for patients with NPC. In recent years, with the development and application of comprehensive treatment and Intensity Modulated Radiation Therapy (IMRT) technology, the overall prognosis of nasopharyngeal carcinoma has been significantly improved, 5-year survival rate was 74.5% , 3 -year local control rate was 90%[2]. Despite such aggressive treatment, many patients with locally advanced NPC still develop locally recurrent disease [3].Since local control is directly related to patient’s morbidity and mortality in NPC, there is a strong requirement to develop a method for improving current treatments’ efficacy.  One strategy to improve local control is escalating the dose of radiotherapy. This is because local control has been shown to be directly related to the radiotherapy dose . Several techniques, including brachytherapy , stereotactic radiosurgery , and dose-painting intensity modulated radiotherapy (IMRT) , have been used to increase radiotherapy dose. However, due to the large number of critical anatomic structures near the nasopharynx, dose-escalation in NPC can also lead to increased toxicities . One of the more effective techniques is the simultaneous modulated accelerated radiation therapy (SMART) IMRT technique [10]. It delivers both accelerated radiotherapy and hypofractionated radiotherapy to the GTV. The main challenge for these treatments is to identify the appropriate tumor volume that could be received the high-dose radiotherapy. Conventional dose-escalation is conducted via using computed tomography (CT) to identify the gross tumor volume (GTV). However, recent progress in the field of ﬂuorine-18-ﬂuorode-oxyglucose positron emission tomography/computed tomography (18F-FDG-PET/CT)-adjuvant treatment planning allows more accurate tumor volume delineation ]. Thus, we hypothesize that of 18F-FDG-PET/CT-adjuvant treatment planning can improve dose-escalation radiotherapy for NPC, which in turn can improve therapeutic efficacy as well as reducing toxicity.  To identify this hypothesis, we compared the efficacy and toxicity of three treatments, including conventional chemoradiotherapy, CT-guided dose-escalation chemoradiotherapy and PET/CT guided dose-escalation chemoradiotherapy, in patients with locally advanced NPC via a randomized clinical trial in our department. PET-CT fusion may have significant impact on staging and radiotherapy treatment delineation in NPC. PET/CT-guided dose escalation radiotherapy appears to be well-tolerated. The SMART-IMRT technique to enhance BED of GTV, combined with concurrent chemotherapy, is completely feasible for local advanced NPC.  [1] Wei WI, Sham JS. Nasopharyngeal carcinoma. Lancet. Jun 11-17 2005;365(9476):2 041-2054.  [2] Lu H, Peng L, Yuan X, Hao Y, et al.Concurrent chemoradiotherapy in locally advanced nasopharyngeal carcinoma: a treatment paradigm also applicable to patients in Southeast Asia. Cancer Treat Rev. 2009, 35 (4):345-353.  [3] Wee J, Tan EH, Tai BC, et al. Randomized trial of radiotherapy versus concurrent chemoradiotherapy followed by adjuvant chemotherapy in patients with American Joint Committee on Cancer/International Union against cancer stage III and IV nasopharyngeal cancer of the endemic variety. J Clin Oncol. 2005;23(27):6730-6738.  [4] Marks JE, Bedwinek JM, Lee F, Purdy JA, Perez CA. Dose-response analysis for nasopharyngeal carcinoma: an historical perspective. Cancer. Sep 15 1982;50(6):1042-1050.  [5] Teo PM, Leung SF, Tung SY, et al. Dose-response relationship of nasopharyngeal carcinoma above conventional tumoricidal level: a study by the Hong Kong nasopharyngeal carcinoma study group (HKNPCSG). Radiotherapy and oncology : journal of the European Society for Therapeutic Radiology and Oncology. Apr 2006;79(1):27-33.  [6] Teo PM, Leung SF, Lee WY, Zee B. Intracavitary brachytherapy significantly enhances local control of early T-stage nasopharyngeal carcinoma: the existence of a dose-tumor-control relationship above conventional tumoricidal dose. International journal of radiation oncology, biology, physics. Jan 15 2000;46(2):445-458.  [7] Hara W, Loo BW, Jr., Goffinet DR, et al. Excellent local control with stereotactic radiotherapy boost after external beam radiotherapy in patients with nasopharyngeal carcinoma. International journal of radiation oncology, biology, physics. Jun 1 2008;71(2):393-400.  [8] Lin S, Pan J, Han L, et al. Nasopharyngeal carcinoma treated with reduced-volume intensity-modulated radiation therapy: report on the 3-year outcome of a prospective series. Int J Radiat Oncol Biol Phys. 2009; 75(4):1071-8.  [9] Ashamalla H, Guirgius A, Bieniek E, et al. The impact of positron emission tomography/computed tomography in edge delineation of gross tumor volume for head and neck cancers [J]. Int J Radiat Oncol Biol Phy, 2007, 68 (2):388-395.  [10] Butler EB, Teh BS, Grant WH, 3rd, et al. Smart (simultaneous modulated accelerated radiation therapy) boost: a new accelerated fractionation schedule for the treatment of head and neck cancer with intensity modulated radiotherapy. International journal of radiation oncology, biology, physics. Aug 1 1999;45(1):21-32.  [11] Madani I, Duthoy W, Derie C, et al. Positron emission tomography-guided, focal-dose escalation using intensity-modulated radiotherapy for head and neck cancer. International journal of radiation oncology, biology, physics. May 1 2007;68(1):126-135.  . | | |
| 9.2 | Aim of study: | | |
|  | This pilot trial is designed to determine whether PET/CT-guided radiotherapy dose escalation can improve local control while minimizing toxicity for the treatment of locally advanced nasopharyngeal carcinoma. | | |
| 9.3 | Hypothesis (e.g. *Compared to x control, y intervention leads to a greater rate of z outcome.*) | | |
| PET/CT-guided dose escalation radiotherapy is well-tolerated for patients with locally advanced NPC as compared to conventional chemoradiotherapy. | | |
| 9.4 | Primary outcome(s) | Outcome measure(s) | Time-point |
| Local progression-free survival (LPF） | 3-year |
|  |  |
| 9.5 | Secondary outcome(s) | Disease-free survival (DFS) | 3-year |
| Overall survival (OS) | 3-year |
| Short term toxicity | 3-month |
| Long term toxicity | 3-year |
|  |  |
| 9.6 | In what way will the research contribute to knowledge or healthcare development? | | |
|  | The project findings will be published in the form of paper, to be published 2-4 papers. The results of this study will be used on the clinical. | | |

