**10. Study subjects**

| 10.1 | Inclusion criteria: |
| --- | --- |
| Patients with previously untreated Stages III and IVA (AJCC 6th Edition) of locally advanced NPC, and histologically confirmed NPC by biopsy, no evidence of distant metastasis, Karnofsky performance status≥70, and good bone marrow, liver and kidney function (white blood cell count ≥ 4.0×109/L, platelets ≥ 100×109/L, albumin ≥30 g/L, creatinine ≤100μmol/L). Ages eligible for study: 18 yeas to 70 years. Patients those with a prior (within 5 years) or synchronous malignancy were excluded. |
| 10.2 | Exclusion criteria: |
| There was evidence of distant metastases, previous malignancy or other concomitant malignant disease, pregnant or lactating, nasopharyngeal radiotherapy history, patients withdrew during treatment or doctor and other factors caused by violation of the study protocol. |
| 10.3 | Sample-size and rationale for calculation: |
| Sample-size= 90 ﹡  Based on the following rationale: To detect 3-year local progression-free survival (LPF） with a two-sided 5% significance level and a power of 80%, a sample size of 30 patients per group was necessary, given an anticipated dropout rate of 10%. |
| 10.4 | Number of subjects to be recruited locally in relation to this application: |
| n= 90 ﹡in applying site. |
| 10.5 | How will subjects to be identified and recruited? |
| We will publish the recruitment information of clinical trials on the website of Xuzhou Medical College Hospital (***http://www.jsxyfy.com/***). According to the specific inclusion criteria and exclusion criteria rigorous screening patients. |

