**13. Methods of Statistical Analysis**

| All events were measured from the date of randomization. OS was defined as the time from the date of radiotherapy to death or the latest date known to be alive. Durations were calculated from the end of treatment. The Kaplan-Meier method was used to calculate the actuarial rates of local control, DFS and OS. The χ2 test was used to compare incidence rates and categorical variables and Student’s t-test was used to compare the means of continuous variables, designated to be significant at p<0.05. |
| --- |

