**14. Potential Risk Arising from Study**

| 14.1 | Induce discomfort or distress | Yes |
| --- | --- | --- |
| 14.2 | More invasive than the usual management | No﹡ |
| 14.3 | Increase physical or psychological risk | No |
| 14.4 | Involve a potential toxin, mutagen or teratogen | No |
| 14.5 | Involve radiation or radioactive substance | Yes |
| 14.6 | Incur other hazards | No |
| 14.7 | If yes to any of the above, provide details: | |
| Item 14.1.The most common acute toxicities were mucositis, with 52.4% to 54.6% grade 2 toxicity and 28.6%~31.8% grade 3 toxicity. Late toxicities were grade 1-2 skin dystrophy, subcutaneous fibrosis, xerostomia, and hearing loss. No patient had grade 4 late toxicity.  Item 14.5. Radiation therapy itself involves radiation. The use of 18F-FDG-PET/CT may slight impact on the surrounding environment, especially in the patient's excreta. | |
| 14.8 | Significant difference(s) from usual management: | |
|  | PET/CT-guided dose escalation radiotherapy is well-tolerated for patients with locally advanced NPC as compared to conventional chemoradiotherapy. | |

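### Section 9.3 claims comparative tolerability, but the only method given for incidence rates is a chi-square test of difference at p<0.05, and a non-significant result of that test cannot support the claim

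*Protocol*

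**What the plan says.** Section 9.3 of the protocol holds a single hypothesis: "PET/CT-guided dose escalation radiotherapy is well-tolerated for patients with locally advanced NPC as compared to conventional chemoradiotherapy". Toxicity is a secondary outcome in section 9.5, listed as "Short term toxicity" at 3 months and long-term toxicity at 3 years.

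Section 13 gives the method for rates: "The χ2 test was used to compare incidence rates and categorical variables", with tests "designated to be significant at p<0.05". Section 7 repeats this. Neither section says which test result would bear out the hypothesis in 9.3.

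Section 10.3 sets the size for 3-year local progression-free survival at a "two-sided 5% significance level and a power of 80"%, and says that "a sample size of 30 patients per group was necessary, given an anticipated dropout rate of 10"%. Section 9.1 describes the comparison as one of three arms: "we compared the efficacy and toxicity of three treatments". No power or precision is given for toxicity.

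Section 14.7 gives acute mucositis as "52.4% to 54.6% grade 2 toxicity and 28.6%~31.8% grade 3 toxicity", without naming an arm. Section 14.8, a field for differences from usual management, repeats the 9.3 hypothesis as a plain statement.

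**The concern.** To say that an escalated treatment is well tolerated relative to a control is to say that any excess toxicity is small enough to accept. A test of difference takes no excess as its null hypothesis. Significance can show harm or benefit, but non-significance shows only that the data did not separate the arms. In a small trial non-significance is likely whether or not a material excess exists.

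So the one hypothesis in 9.3 and the one method in section 13 do not fit together. The protocol fixes both, so this is a mismatch between two stated elements and not a detail left for an analysis plan.

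The stake is a falsely reassuring safety statement about dose escalation given with chemotherapy. Section 9.1 itself warns that escalation in this disease can raise toxicity, and section 9.6 expects the results to be used clinically.

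**Working it through.** **Inputs**
- Arm size: 30 per group (10.3). With the stated 10% dropout, 30 × 0.9 = 27. That dropout was stated for the 3-year outcome, so 30 is the nearer figure for 3-month toxicity and 27 is the cautious one.
- Test: two-sided 5% chi-square without continuity correction. Section 13 gives p<0.05; two-sidedness is taken from 10.3; no correction is mentioned.
- Control rate of grade 3 mucositis: about 30%. This is an assumption, because the range 28.6% to 31.8% in 14.7 is not attributed to an arm. It is varied below from 10% to 40%.
- True excess: 20 points. This is our illustration and is not in the protocol.

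**The plan's own figure.** There is none for toxicity to reproduce. The 30 per group is for local progression-free survival, with no effect size stated.

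**Power for 30% versus 50%, normal approximation**

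Power = Φ[(d − 1.96 × SE0) / SE1], where SE0 = √(2 × 0.4 × 0.6 / n) and SE1 = √((0.3 × 0.7 + 0.5 × 0.5) / n).
- n = 30: SE0 = 0.1265, SE1 = 0.1238; (0.20 − 0.2479) / 0.1238 = −0.387; power 34.9%.
- n = 27: SE0 = 0.1333, SE1 = 0.1305; (0.20 − 0.2613) / 0.1305 = −0.470; power 31.9%.

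**Exact check**, summing the two binomial distributions over all outcomes that the chi-square test rejects:

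| Control → escalated | n = 30 | n = 27 |
|---|---|---|
| 30% → 40% | 12% | 12% |
| 30% → 50% | 35% | 31% |
| 30% → 60% | 66% | 59% |
| 28.6% → 48.6% | 35% | 32% |
| 31.8% → 51.8% | 35% | 30% |
| 10% → 30% | 50% | 49% |
| 20% → 40% | 39% | 38% |
| 40% → 60% | 35% | 29% |

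With a Yates correction or Fisher's test, power for a 20-point rise from the 14.7 rates falls to about 26% (n = 30) and 22-23% (n = 27).

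**Smallest rise detectable with 80% power** from the 14.7 rates, by the normal approximation: about 35.5 points at n = 30 and 37.5 at n = 27. Detecting 20 points with 80% power needs 92 to 95 per arm.

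**Precision with equal rates of 30%.** Half-width = 1.96 × √(2 × 0.3 × 0.7 / n) = 23.2 points (n = 30) or 24.4 points (n = 27). Identical observed rates would therefore still be compatible with an excess of more than 20 points.

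**What a margin rule could achieve.** With equal true rates, one-sided 2.5% and 80% power, an illustrative 20-point limit needs 81 to 86 per arm.

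**The case against.** Four objections have force.

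1. **The decision rule is an inference.** A reader might conclude that the investigators will read p≥0.05 as proof of tolerability. The protocol nowhere says so, and section 13 does not name tolerability. What stands is narrower: the hypothesis is comparative tolerability, the only method stated for rates is a difference test, and nothing links the two.

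2. **Toxicity is framed differently elsewhere.** Sections 7 and 9.1 hypothesise a reduction in toxicity, and section 9.2 speaks of minimising it. A difference test suits a claim of reduction. It does not suit 9.3, and even for a fall from 30% to 10% the exact power is only about 50% at 30 per arm and 49% at 27.

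3. **This is a pilot, Phase II trial sized for another outcome.** Low power for a secondary safety outcome is expected and is not in itself a fault. It argues for estimates with intervals, and it makes a comparative conclusion drawn from non-significance less safe.

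4. **The headline figure is conditional.** The 30% rate is not stated to be the control rate, and the 20 points are ours. Missing such a rise about two times in three is specific to control rates near 30% or above; at 10% it is about one in two. No rate from 10% to 40% gives better than even odds of detection.

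It would also be too strong to say that the protocol reports the hypothesis as already proven throughout. Sections 7, 9.1 and 15 say only that the treatment appears to be well tolerated, which is hedged and not comparative. Only 14.8 states the comparative claim flatly.

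**Conclusion.** The mismatch is real and should be corrected. As written, the method in section 13 could reveal a large excess of toxicity in the PET/CT-guided arm, but it could not establish the tolerability that 9.3 asserts. For a 20-point rise from a control rate near 30%, power is about 35% at 30 per arm and 30-32% at 27. Over control rates of 10% to 40% it is about 50% to 35% and 49% to 29% respectively. These figures assume equal arms, an uncorrected chi-square test, and a rise chosen for illustration.

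The documents do not support going further and saying that the plan has adopted non-significance as its criterion. The finding is that no stated method can carry the claim.

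**What to change.** - **Sections 9.3 and 13:** treat tolerability as estimation. Report grade 3 or higher toxicity rates by arm, acute and late separately, and the PET/CT-escalation minus control difference for each with its 95% confidence interval.
- **Section 13:** state that p≥0.05 is not evidence of tolerability. Allow a conclusion of *well tolerated compared with conventional treatment* only if the upper confidence bound lies below an excess that the investigators fix before outcome data are seen. Otherwise report relative tolerability as inconclusive. The size of that excess is for the investigators to choose.
- **Section 14.8:** remove the hypothesis stated as fact. This is a secondary drafting change.

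The cost is some wording and two confidence intervals, with no extra patients or data. The downside is that at about 30 per arm the trial will probably have to call relative tolerability inconclusive. With a half-width of 23 to 24 points, even a 20-point limit would be met only if observed toxicity were roughly 3 to 4 points lower with escalation than with control (20 − 23.2 = −3.2; 20 − 24.4 = −4.4). For that reason the estimates and intervals are the core of the change, and the upper-bound rule is a guard on wording.

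### Three-year late toxicity falls by default to a chi-square test on crude incidence rates, which cannot handle patients lost or dead before 3 years; the bias can go either way and is small

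*Protocol*

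**What the plan says.** Protocol item 9.5 lists "Long term toxicity" among the secondary outcomes and sets its time-point: "Long term toxicity | 3-year". DFS and OS are secondary outcomes at the same time-point, and local progression-free survival is the 3-year primary outcome (item 9.4).

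Section 13 divides the methods in two. On time-to-event outcomes: "The Kaplan-Meier method was used to calculate the actuarial rates of local control, DFS and OS". On the rest: "The χ2 test was used to compare incidence rates and categorical variables". The lay summary in item 7 repeats the division: "The χ2 test was used for comparing incidence rates and categorical variables". Student's t-test is reserved for means.

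Item 10.3 sets 30 patients per group, "given an anticipated dropout rate of 10" per cent. Item 10.2 lists withdrawal during treatment and protocol violation among the exclusions. The protocol does not say how a patient who dies or is lost before 3 years enters a late-toxicity rate.

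**The concern.** Late toxicity accrues over time, and a patient can show it only while alive and under assessment. A chi-square test needs every patient classed as with or without toxicity, or removed. Someone who dies or is lost at 18 months without toxicity fits none of these well. The protocol recognises this for its other 3-year outcomes by using Kaplan-Meier, but not for this one.

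Tolerability is the trial's stated hypothesis (item 9.3), and the aim in item 9.2 pairs better local control with less toxicity. A late-toxicity rate that depends on an unstated denominator, and on how completely each arm is followed, is a weak basis for that claim. The denominator could also be settled after the results are known.

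**Working it through.** The protocol states no late-toxicity figure, so there is none to reproduce. Its 30 per group relates to local progression-free survival and is a separate matter.

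**Inputs**
- 5-year survival 74.5% (item 9.1, a background figure for the disease).
- Dropout 10% (item 10.3), taken here as loss by 3 years. This is an assumption.
- 30 patients per arm (item 10.3).
- 3-year late-toxicity risk if nobody died or was lost: not given. Assumed 30%, range 20% to 50%.
- Constant, independent hazards of toxicity, death and loss. This is an assumption.

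**Step 1: expected follow-up.** 3-year survival = 0.745^(3/5) = 0.838, so 16.2% die, or 30 × 0.162 = 4.9 patients per arm. Alive and still followed: 0.838 × 0.90 = 0.754, or about 23 of 30.

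**Step 2: three ways to report the same data.** Cumulative hazards over 3 years at 30% toxicity are A = −ln 0.70 = 0.357 (toxicity), D = −ln 0.838 = 0.177 (death) and L = −ln 0.90 = 0.105 (loss). The sum T is 0.639, and e^(−T) = 0.528.
- Crude, all patients counted: (A/T)(1 − e^(−T)) = (0.357/0.639)(0.472) = 26.4%.
- Cumulative incidence, death competing: [A/(A+D)](1 − e^(−(A+D))) = (0.357/0.533)(0.413) = 27.6%.
- Dead or lost without toxicity left out: crude/(crude + e^(−T)) = 0.264/(0.264 + 0.528) = 33.3%.

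| Assumed risk | Crude, all counted | Cumulative incidence | Dead or lost left out |
|---|---|---|---|
| 20% | 17.5% | 18.4% | 22.5% |
| 30% | 26.4% | 27.6% | 33.3% |
| 50% | 44.3% | 46.3% | 54.0% |

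The denominator alone moves the rate by 5 points (22.5 − 17.5) to about 10 points (54.0 − 44.3).

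**Step 3: loss separated from death.** With L = 0 the first formula becomes the second, so for death alone the crude proportion equals the cumulative incidence (27.6% at 30% risk). The remaining shortfall in the table, about 1 to 2 points, is due to loss. If loss were 5% in one arm and 20% in the other, with identical toxicity and survival, the crude rates would be 27.0% and 25.0%, while the cumulative incidence is 27.6% in both.

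**Step 4: survival differing between arms, same toxicity hazard, 10% loss.**
- Survival 83.8% against 95%, risk 30%: crude 26.4% against 27.9% (gap 1.5 points); cumulative incidence 27.6% against 29.3% (gap 1.6 before rounding).
- The same survival, risk 50%: crude 44.3% against 46.7% (gap 2.4); cumulative incidence 46.3% against 48.9% (gap 2.6).
- Survival 90% against 70%, risk 30%: crude 27.2% against 24.4%. With the dead or lost left out it is 32.4% against 35.6%, so the direction reverses.

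The death-driven gap therefore persists under cumulative incidence, and so under Gray's test. A cause-specific log-rank test compares toxicity hazards, which are equal here by construction.

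**Step 5: scale.** The standard error of a difference at 30 per arm is √(0.264 × 0.736/30 + 0.279 × 0.721/30) = 0.115. For 44.3% against 46.7% it is √(0.443 × 0.557/30 + 0.467 × 0.533/30) = 0.129. A gap of 1 to 3 points is well inside 11 to 13 points.

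**The case against.** A reader might infer that late toxicity will be understated, to the advantage of the arm with more early deaths. The documents do not support a direction. It holds only if every patient stays in the denominator, and it reverses if those dead or lost without toxicity are dropped. Nor does it clearly help the escalated arm: if escalation improves local control and survival as hoped, that arm would have fewer deaths, and the all-patients rate would count against it.

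The 26.4% against 30% is also not all error. The 30% is the risk with deaths removed; against the competing-risk target of 27.6% the shortfall is only the part due to loss.

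Three further objections have weight. The use of chi-square for toxicity is inferred. Denominators for a secondary safety outcome are often left to an analysis plan, which is not shown. The distortion is small beside sampling error, and smaller still if toxicity appears early: with all onset in year 1 and 30% risk, the crude rates at 90% and 70% survival are 29.0% and 27.9%.

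These points limit the size and direction but do not remove the concern. The protocol does more than stay silent: it names its methods and gives an actuarial one to its other 3-year outcomes, leaving late toxicity with a test that cannot use partial follow-up.

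**Conclusion.** The concern holds in a limited form. By inference from items 7 and 9.5 and section 13, 3-year late toxicity would be compared on crude proportions, although on the protocol's own figures about a quarter of each arm would not be alive and followed to 3 years. The reported rate could lie about 1 to 2 points below the cumulative incidence or about 4 to 8 points above it (22.5 − 18.4 to 54.0 − 46.3), depending on the denominator. Loss to follow-up is the clear source of bias, and it distorts the comparison if it differs between arms. The effect of death is a choice of estimand.

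The sizes rest on assumed toxicity risks of 20% to 50%, constant hazards, dropout read as loss by 3 years, and a background survival figure that is not specific to any arm. At 30 patients per arm this is a low-priority improvement and does not threaten the trial's validity.

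**What to change.** In section 13, name late toxicity and analyse it as time to first qualifying late event among all treated patients, censored at last assessment. Report the 3-year cumulative incidence with death as a competing event, and the number still under assessment at 3 years in each arm. Compare arms with a cause-specific log-rank test, censoring deaths, because Gray's test would carry the death-driven gap into the comparison. Keep chi-square or exact tests for 3-month toxicity, where little follow-up is missing.

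The cost is a few sentences of analysis text and recording the visit at which each late toxicity is first seen. The protocol text gives no follow-up visit schedule, so the sponsor should confirm that assessments are frequent enough to date onset. The log-rank test also assumes that loss and death are unrelated to toxicity risk, which should be stated.
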